# A pragmatic randomized controlled trial of standard care versus corticosteroids plus standard care for treatment of pneumonia in adults admitted to Kenyan hospitals (SONIA)

**DOI:** 10.12688/wellcomeopenres.18401.2

**Published:** 2025-05-28

**Keywords:** Pragmatic, Randomized-Controlled Trial, Steroids, Pneumonia, Adults, Mortality, Africa

## Abstract

**Background:**

Mortality among adults admitted to hospital with community acquired pneumonia in resource-limited settings is high. Recent studies conducted in high-income settings have demonstrated beneficial effects of low-dose corticosteroids in reducing mortality in patients with severe community acquired pneumonia. It is unknown whether these findings apply to low-income settings such as sub-Saharan Africa.

This pragmatic randomized-controlled open-label trial will determine the effect of adjunctive low-dose corticosteroids in the management of adults admitted to hospital with community acquired pneumonia on mortality 30-days post-randomization.

**Methods:**

We will enroll and randomize 2180 patients admitted with a diagnosis of community acquired pneumonia into two arms: the control and intervention arm. Those in the control arm will receive standard care for the treatment of community acquired pneumonia i.e., combination therapy with a beta-lactam and macrolide antibiotic. Those in the intervention arm will receive up to 10-days treatment with low-dose oral corticosteroids in addition to standard care. All participants will be followed up to 30- days post randomization and their final status recorded (alive or dead).

**Discussion:**

If adjunctive low-dose oral corticosteroids are found to be beneficial, this easily scalable intervention would significantly reduce the currently high mortality associated with community acquired pneumonia.

Pan-African Clinical Trials Registry: PACTR202111481740832; ISRCTRN registry: ISRCTN36138594

## Introduction

### Background and rationale {6a}

Community acquired pneumonia (CAP) is a common cause of illness and death among adults in Kenya and other low and middle-income countries (LMICs)
^
1
^. The pattern of CAP in sub-Saharan Africa differs from that in other regions due to higher prevalences of coinfections like pulmonary tuberculosis and HIV and differences in risk factors for severe disease in this population compared to others
^
2
^.

Inflammation plays an important role in the pathophysiology of pneumonia with elevated levels of inflammatory cytokines and infiltration of interstitial lung tissue with various inflammatory cells being observed in patients with severe disease
^
3
^. Dysregulated inflammation results in a sepsis-like syndrome with eventual organ dysfunction in severe cases
^
4
^.

Corticosteroids have a role in improving patients outcomes in CAP by modulating the release of inflammatory mediators such as cytokine and reducing pulmonary inflammation
^
5
^. While previous data on the effect of corticosteroids in the management of CAP have been inconclusive
^
6–
9
^, data from the RECOVERY trial during the COVID-19 pandemic
^
10
^ and other studies such as the ESCAPe
^
11
^ and CAPE COD
^
12
^ trials have demonstrated a beneficial effect of adding corticosteroids to the management of patients admitted with severe CAP. Consequently, several systematic reviews and metanalyses now report corticosteroids have beneficial effects in reducing progression to invasive ventilation, duration of hospital stay and mortality
^
13–
16
^.

These studies are however potentially not applicable to settings such as Kenya for the following reasons; a) mortality in this setting is ~30%, which is much higher than that observed in studies in high income settings, b) patients in our setting are younger (35–50 years) compared to average age of 65 years in other settings c) the prevalence of comorbidities (e.g. HIV and TB) in patients with CAP in LMIC settings is different. Without evidence from a sub-Saharan African population, questions remain on the effectiveness of adjunctive corticosteroids in the management of patients admitted with severe CAP in the region.

 We are conducting a pragmatic randomized controlled open-label clinical trial to test if there is a survival benefit in the use of adjunctive low-dose corticosteroid therapy in patients admitted to hospital with CAP.

## Objectives {7}

Primary Objectives

To determine if there is a difference in the proportion of patients with community acquired pneumonia that die within 30 days of being randomized to receive adjunctive corticosteroid treatment compared to those that are randomized to receive standard treatment only

Secondary Objectives

To determine if there is a difference in the proportion of patients with community acquired pneumonia that die within seven, 14 and 21 days of being randomized to receive adjunctive corticosteroid treatment compared to those that are randomized to receive standard treatment onlyTo determine if there is a difference in the proportion of patients with community acquired pneumonia that die in hospital and out of hospital after being randomized to receive adjunctive corticosteroid treatment or standard treatment for community acquired pneumonia onlyTo determine the correlation of pre-existing and treatment induced changes in the participants’ immune and metabolic profiles with study outcomes by trial arm

## Trial design {8}

We will conduct a pragmatic open label randomized controlled clinical trial. Eligible participants will be recruited from the in-patient adult medical wards of the participating hospitals. Patients admitted to the general wards as well as the High Dependency Units (HDU) and Intensive Care Units (ICU) will be eligible to join the trial and will be identified by the attending clinician and a study clinician.

Participants enrolled into the trial will be randomized 1:1 to either receive standard of care for CAP or standard of care plus a 10-day course of low-dose oral corticosteroids. A subset of all recruited participants, about 50 per trial arm, will be further randomized to have a blood draw at four timepoints during their participation. For these participants, a 10 ml blood sample will be collected at enrollment, 24, 48 and 72 hours after enrollment for an immunology sub study.

All participants will be followed up to their 30
^th^ day after enrollment to determine their vital status. The median duration of hospital admission for patients with CAP in the participating hospitals is 4 days, therefore having the primary outcome ascertained at 30 days is unlikely to result in misclassification of patients where some are recorded as being alive only to die a few days later.

Being a pragmatic trial, the study will not interfere with any procedure, investigations, or treatments that the attending clinicians administer to participants. However, all treatments received will be recorded.

## Methods: Participants, interventions and outcomes

### Study setting {9}

The proposed study will be conducted within the Clinical Information Network (CIN), and five other hospitals. The CIN is a collaborative effort between KEMRI-Wellcome Trust Research Programme, Kenya Paediatric Association (KPA), Kenya’s Ministry of Health (MoH), and several county hospitals
^
17–
19
^. CIN, which commenced in 2013, initially sought to improve the care provided to in-patient children and sick new-borns through improving the collection and use of information obtained from routine medical records. At the onset of the COVID-19 pandemic, it expanded to the adult wards to conduct surveillance on severe acute respiratory illness (SARI) and now includes collection of routine data from adult wards. A total of 24 hospitals are currently part of the CIN. Use of de-identified routine data obtained from the CIN hospitals for observational research has been approved by the Kenya Medical Research Institute Scientific and Ethics Review Unit (KEMRI SERU).

The trial will recruit participants at the following 15 hospitals which are part of CIN: Bungoma County Referral Hospital, Busia County Referral Hospital, Embu Level 5 Teaching and Referral Hospital, HomaBay County Referral Hospital, Jaramogi Oginga Odinga Teaching and Referral Hospital, Kakamega County General Hospital, Kiambu Level 5 Hospital, Kisii Teaching and Referral Hospital, Kisumu County Hospital, Kitale County Referral Hospital, Machakos Level 5 Hospital, Mama Lucy Kibaki Hospital, Mbagathi County Hospital, Naivasha Level 5 Hospital and Nakuru County Referral Hospital (
Figure 1). Five other hospitals that are trial sites but are not part of CIN include Coast General Teaching and Referral Hospital, Kenyatta National Hospital, Kenyatta University Teaching and Referral Hospital, Kilifi County Hospital, and Moi Teaching and Referral Hospital, Eldoret (
Figure 1).

**Figure 1. f1:**
[figure not shown]
Map of Kenya showing distribution of SONIA trial sites. This figure represents the distribution of SONIA trial sites. Eight sites are located in western Kenya, eight around central Kenya and two are at the Kenyan coast.

### Eligibility criteria {10}

We will recruit patients who have been admitted to hospital with a diagnosis of community acquired pneumonia and for whom COVID-19 results are either negative or unknown. Diagnosis of CAP will be based on clinical criteria recommended by the world health organization (WHO)
^
20,
21
^ and described in detail in the inclusion criteria below. Unless there are specific reasons justifying exclusion from the study as detailed in section on inclusion and exclusion criteria, we will not exclude patients which conditions such as HIV, diabetes mellitus or other presenting conditions except those indicated below.

### Inclusion criteria

Adults aged 18 years or overAdmitted to hospital with a diagnosis of community-acquired pneumonia. Pneumonia will be based on a clinical definition as follows: the presence of at least 2 of the following signs and symptoms for less than 14 days: cough, fever, dyspnea, hemoptysis, chest pain or crackles on chest examination
^
20,
21
^.Admitted to hospital within the previous 48 hours in this current illnessProvides written informed consent

### Exclusion criteria

Diagnosis of COVID-19 confirmed via polymerase chain reaction (PCR) of nasopharyngeal/oropharyngeal (NP/OP) swabs or antigen rapid diagnostic tests (RDTs) done at the hospital. This criterion only applies if the test result is known at the point of enrollmentHospital acquired pneumonia- defined as pneumonia in a patient who has been in hospital for >48 hours who did not have the symptoms at admission
^
21
^
Known or suspected condition which in the opinion of attending clinician requires treatment with corticosteroids, including but not limited to chronic obstructive pulmonary disease, asthma, adrenal insufficiency, Pneumocystis Jirovecii pneumonia (PCP).If the clinician strongly suspects COVID-19 and wants to provide corticosteroids to the patient because of this suspicion, then the patient will be excluded from the trial.Pregnancy or breast feedingAny contraindication to corticosteroid administration

### Who will take informed consent? {26a}

The trial has a study clinician (non-degree trained, referred to as clinical officer in Kenya) posted to each of the hospitals, who will recruit participants, act as a local facilitator to reinforce compliance with the study protocol, and also obtain informed consent. The clinical officer will seek written informed consent from all eligible patients. Deferred written informed consent will be sought from patients if the patient is too unwell to provide consent within the first 48-hours of admission. This process, commonly implemented in clinical trials taking place in emergency situations
^
6
^, entails a short verbal assent process from legally authorized representatives (LARs) at the time of enrolment by a trained study staff followed later by full written consent after the patient’s condition improves (within 48 hours of recruitment). The information given during this verbal assent process includes key elements of the International Conference on Harmonization Good Clinical Practice (ICH-GCP) recommendations. For patients who die prior to the obtaining full written consent, assent will be used as permission to be included in the trial and use of their data. A copy of the consent form and participant information sheet (PIS) will be provided to the patient or LAR.

### Additional consent provisions for collection and use of participant data and biological specimens {26b}

Written informed consent will be sought from all participants for the use of their data and blood samples, where applicable, for future studies.

## Interventions

### Explanation for the choice of comparators {6b}

The intervention, adjunctive low-dose corticosteroids, is being compared to the current standard of care treatment. While a placebo control could have been used, this would be difficult to implement in the context of a pragmatic trial. Having a mortality end point mitigates against any shortcomings arising from the lack of a placebo control group.

### Intervention description {11a}

Trial participants will be randomized 1:1 to either of the two trial arms; standard care for community acquired pneumonia alone (control arm) or standard care plus a 10-day course of low-dose oral corticosteroids (intervention arm).

Participants randomized to the control arm will receive treatment according to local and WHO guidelines for CAP which currently recommend a beta lactam antibiotic and a macrolide for 7–14 days
^
22
^. In order to minimize variability in the standard treatment offered at the different hospitals, the study team will provide hard copies of the treatment guidelines, as we have demonstrated that this is associated with better adherence
^
23
^. In the event of stockouts of standard treatment, the trial will procure the medications for study patients as prescribed by the treating physician, and in accordance with trial treatment allocation. No further interventions will be made in this pragmatic clinical trial.

Participants who are randomized to the intervention arm will receive the standard care treatment for CAP as outlined above and any of the equivalent doses of corticosteroids listed in
Table 1 for a period of 10 days. The study will provide the corticosteroids for all participants in the intervention arm based on local availability. The corticosteroids will be administered orally, including via nasogastric tube for patients on ventilation or otherwise unable to take the medications orally.

**Table 1. T1:** Corticosteroids to be used in the trial. This table details the corticosteroids being used as the trial intervention. The corticosteroid doses represented in the table are bioequivalent.

Corticosteroid	Once daily dose
Dexamethasone	6mg
Betamethasone	5mg
Hydrocortisone	160mg
Methylprednisolone	30mg
Prednisolone	50mg
Prednisone	50mg

All other care will be determined by the clinical team primarily responsible for the patient’s care.

### Criteria for discontinuing or modifying allocated interventions {11b}

During participation, the trial intervention may be stopped, and the participant withdrawn for the following reasons:

The participant’s attending physician may withdraw the study drug in those randomized to the intervention arm due to side effect/s or if the corticosteroids seem to cause worsening of a participant’s existing condition(s). Additionally, they may recommend administration of corticosteroids to a participant randomized to the control arm if in their opinion such a participant requires a corticosteroid as part of their care. Changes in treatment and reasons for change will be captured into the database in such casesIf a participant tests positive for COVID-19 after joining the trial and undergoing randomization, they will be withdrawn from the trial. This is because there will no longer be meeting the eligibility criteria, in addition to loss of equipoise since they will require to be on corticosteroids.If a participant requests to be withdrawn from the trial and was in the intervention arm, the corticosteroids will be discontinued and the participant withdrawn from the trial.

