## Statistical methods

### Statistical methods for primary and secondary outcomes {20a}

The primary analysis will be an intention to treat analysis in which we will compare outcomes between all patients randomized to the two study arms, irrespective of whether they receive their allocated treatment. For the primary outcome of 30-day mortality, we will use the unadjusted hazard ratio determined from Cox regression to estimate the mortality rate ratio between the treatment groups. If we detect any imbalances in potential confounders at baseline (such as age, sex, severity of illness, study site), then an adjusted Cox model will be used. If losses to follow-up do occur, patients will be censored at time of last assessment. Kaplan-Meier survival curves will be constructed to display cumulative mortality over the 30-day follow-up period.

In the per-protocol analysis we will exclude patients stopping or pausing the study medication at any time point and those withdrawn from the trial.

Complete case analyses will be used for secondary endpoints. For all secondary endpoints, we will calculate unadjusted and adjusted estimates of the effect size and corresponding 95% confidence intervals using linear, logistic, or cox proportional hazards regression as appropriate. All analysis will be done using R (Version 4.4.2, R Foundation for Statistical Computing: Vienna, Austria)

For the immunology outcome, omics data such as proteomic and transcriptomic data generated will be processed in the R programming language as described in section 33. To find genes/proteins whose mean response has significantly changed over the first 72 hours, the processed data will be fitted in a multinomial mixed model predicting the possible outcomes, adjusting for relevant baseline characteristics. The expected outcomes are, survived versus died in the treatment and placebo arms.

To understand the biological response associated with survival, induced/repressed by the treatment, functional analysis of the significant genes/proteins will be explored using R packages such as Clusterprofiller, GSVA and fgsea.

Integrative approaches will be used on the cellular phenotyping, proteomic, transcriptomic, metabolomic data to elucidate the biological processes promoted/repressed by corticosteroid treatment that are associated with survival that could be targeted with additional intervention

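### Withdrawing participants who test COVID-19 positive after randomization can censor their later deaths out of the primary 30-day mortality analysis

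*Protocol article*

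**What the plan says.** Section 11b of the protocol article (criteria for discontinuing or modifying allocated interventions) opens its list with "the trial intervention may be stopped, and the participant withdrawn for the following reasons". Three items follow.

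- **Item 1** covers clinical changes of treatment: the physician may stop the study drug, or give corticosteroids to a control participant. For these, "Changes in treatment and reasons for change will be captured into the database".
- **Item 2** is mandatory. A participant who "tests positive for COVID-19 after joining the trial and undergoing randomization, they will be withdrawn from the trial". Its first reason reads "This is because there will no longer be meeting the eligibility criteria"; its second is loss of equipoise, because the participant will need corticosteroids.
- **Item 3** covers a participant's own request to leave.

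On eligibility, section 10 recruits patients "for whom COVID-19 results are either negative or unknown", and the exclusion list says of confirmed COVID-19: "This criterion only applies if the test result is known" at enrollment.

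On analysis, section 20a makes the primary comparison intention-to-treat over everyone randomized, whatever treatment they took, using a Cox model. It adds: "If losses to follow-up do occur, patients will be censored at time of last assessment". Section 20c defines losses to follow-up to include withdrawals and excludes imputation. The abstract and section 8 promise follow-up of all participants to day 30.

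**The concern.** Neither reason in item 2 supports ending follow-up. A patient whose result was unknown at enrollment met the criteria when randomized, and a later positive result does not undo that. A need for corticosteroids is a treatment matter: intervention participants already receive them, and item 1 already handles a control participant who needs them by recording the change.

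The rule nevertheless removes the person from the trial, not only from the allocated treatment. Censoring in a Cox model is unbiased only if those censored have the same later risk as those who remain, and patients with a new COVID-19 diagnosis may not. The trial is open label and section 8 leaves investigations to attending clinicians, so testing, and with it withdrawal, could differ by arm. Sections 6b and 16c rely on the objectivity of mortality to offset the lack of blinding. That defence weakens if a clinician-ordered test can end ascertainment of the outcome.

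**Working it through.** **1. The route through the text.** Positive test after randomization → withdrawn from the trial (11b, item 2) → counted as a loss to follow-up (20c) → censored at last assessment in the primary model (20a) → not imputed (20c). Nothing shown says that vital status is still collected after withdrawal.

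**2. The plan's own sample size.** Section 14 gives 20% v 15% mortality, two-sided 5%, 85% power, 5% loss and 1,090 per arm.

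- n = [1.960·√(2·0.175·0.825) + 1.036·√(0.20·0.80 + 0.15·0.85)]² / 0.05² = 1,036 per arm.
- 1,036 / 0.95 = 1,091, against 1,090 stated. The figure reproduces, so the issue is bias and not sample-size arithmetic.

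**3. Effect of censoring on the hazard ratio (HR).** The documents give no COVID-19 rates, so every rate here is an assumption.

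- True mortality is p = 20% in both arms (true HR 1.00).
- Death times have density f(t), a truncated exponential on 0–30 days with mean parameter 8 days.
- In arm j a fraction w_j is withdrawn alive, uniformly over days 1–5. A fraction m of them die by day 30, uncounted.
- Counted deaths: d_j(t) = (p − w_j·m)·f(t).
- At risk: Y_j(t) = 1 − ∫₀ᵗ d_j − w_j·U(t), where U is the uniform distribution function on days 1–5.
- The large-sample Cox HR θ solves ∫ [d₁ − (d₁ + d₀)·θY₁/(θY₁ + Y₀)] dt = 0, with 1 = intervention and 0 = control.

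| Withdrawn, intervention v control | m = 10% | m = 14% | m = 20% | m = 40% |
|---|---|---|---|---|
| 1% v 0% | 1.002 | 1.000 | 0.997 | 0.986 |
| 0% v 1% | 0.998 | 1.000 | 1.003 | 1.015 |
| 2% v 1% | 1.002 | 1.000 | 0.997 | 0.985 |
| 1% v 2% | 0.998 | 1.000 | 1.003 | 1.015 |
| 3% v 1% | 1.005 | 1.000 | 0.993 | 0.970 |
| 5% v 0% | 1.012 | 1.001 | 0.983 | 0.926 |
| 0% v 5% | 0.988 | 0.999 | 1.017 | 1.080 |
| Equal rates | 1.000 | 1.000 | 1.000 | 1.000 |

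Censoring is neutral at m of about 14%. That is close to the residual risk of a participant alive at day 3: with F(3) = 0.320, 0.20·(1 − 0.320)/(1 − 0.20·0.320) = 14.5%. Above that value the bias favours the arm with more withdrawals; below it, the other arm. The 5% rows place the plan's whole loss allowance in one arm and are an upper bound.

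**4. Uncounted deaths in one arm.** At 1%: 1,090·0.01·0.10 = 1.1 to 1,090·0.01·0.40 = 4.4. At 5%: 5.5 to 21.8. Expected deaths in an arm at 20% are 1,090·0.20 = 218.

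**5. Against the design effect.** The same model with 15% v 20% and no withdrawal gives HR 0.729. The largest shift at 1% in the intervention arm only is ln 0.986 / ln 0.729, about 5% of the design effect on the log scale. At 5% it is ln 0.926 / ln 0.729 = 24%.

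**6. Power.** Expected deaths after 5% loss are 1,090·0.95·(0.20 + 0.15) = 362. The proportional-hazards HR is ln 0.85 / ln 0.80 = 0.728. If 1% of both arms were withdrawn on top of that loss, with later mortality of 17.5–40%, about 4–8 deaths go uncounted and power (Schoenfeld) stays near 85%. At 5% it is 18–41 deaths and power of 81–84%.

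**The case against.** The loss of deaths is inferred. This is a journal article condensing a fuller protocol, and post-withdrawal data collection is the sort of detail an article may leave out. Other text points towards retention: the intention-to-treat population is everyone randomized, follow-up to day 30 is promised for all, and excluding withdrawn participants from the per-protocol set would be redundant if they were not in the intention-to-treat set.

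The effect is also likely to be small. With about 390 deaths the standard error of the log HR is about 2/√390 = 0.10, so a shift to 0.986 or 1.015 is about 0.15 standard errors. Exposure is limited: patients with COVID-19 known at enrollment are excluded, as are those strongly suspected whom the clinician wants to treat with steroids, and the median stay is 4 days. The rule is the same in both arms, and no text says testing differs by arm. Section 20c already plans to report withdrawals by arm.

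Much of this stands as to size. It does not remove the point. Item 2 is a stated conduct rule, not a gap, and its eligibility reason conflicts with the exclusion list. Nominal membership of the intention-to-treat set keeps a person at risk until censoring but does not count a later death. No analysis plan can recover vital status that sites stopped collecting. The late timing is a fair caution about how much can be retrieved.

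**Conclusion.** The concern holds. The withdrawal rule contradicts the trial's own eligibility criteria and, read with sections 20a and 20c, allows deaths after a COVID-19 withdrawal to drop out of the primary analysis. The text is ambiguous on whether follow-up in fact stopped, so the claim is that deaths can be lost, not that they were.

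The bias is probably small: at most about 1.5% on the HR when withdrawal differs by one percentage point between arms, and nil when rate and later mortality are equal. It could reach 0.926 or 1.080 only in the extreme one-arm 5% case with 40% later mortality. Its direction cannot be set from the documents. These figures rest on the assumed withdrawal rates, timing and mortality above. It should be fixed before the final analysis because it touches the sole primary outcome and can be corrected cheaply.

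The lead-in to 11b is a wording matter only. It could be read as permitting withdrawal for item 1 drug changes, but the rest of the text points to keeping those participants.

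**What to change.** Section “Study status” gives 30 June 2024 as the end of recruitment, so the remedy now lies in data retrieval and analysis.

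- List all withdrawn participants by arm, date and reason.
- For those withdrawn for COVID-19, or for a treatment change if there are any, retrieve day-30 vital status from calls, next of kin or hospital records where consent allows. Analyse them as randomized.
- Censor only for withdrawn consent to follow-up or failed tracing, and report those numbers by arm.
- State in the analysis: *A positive COVID-19 test or a change of treatment after randomization may alter treatment but is not a reason to end vital-status follow-up.* Tighten the 11b lead-in to match.
- COVID-19 positives can still be left out of the per-protocol analysis.

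The cost is tracing work for what may be few people, helped by the three or more contact details per participant planned in section 18b, plus one or two sentences. The sample size is unchanged. Some may be untraceable or have refused contact, so a few may stay censored. If no one was withdrawn for COVID-19, reporting that closes the question.
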